| **SECTION B DETAILS OF THE PROJECT** | | |

| \| **B1** \| \| --- \| | **Please provide a brief summary of the project in simple lay person’s prose outlining the intended value of the project, giving necessary scientific background.**  *(max 500 words)***.**  **Notes**   1. This study extends our recently completed study on transcutaneous vagus nerve stimulation and compassion (The effects of vagus nerve stimulation on compassionate mind training and threat processing; UCL ethics ID: 4277/001). The details below outline how this study extends that work. 2. Testing during any COVID restrictions will strictly follow SLMS GSOP relating to personal contact during the pandemic.   **Background**  This study investigates whether a form of self-affiliation, namely, **self-compassion**, can be modulated using **non-invasive stimulation** of the vagus nerve (**transcutaneous vagus nerve stimulation; tVNS**) via **the external ear** (i.e. earlobe or tragus). The vagus nerve is part of the parasympathetic nervous system (the ‘rest and digest’ system; Murray et al., 2016) and its fibres are spread throughout the upper body, face and neck, including branches that innervate parts of the external ear, close to the skin. Recent research has shown that the vagus nerve is involved in a range of psychological processes including memory, threat/fear processing and positive affect (Kirby et al, 2017; Burger et al. 2016). For example, vagus nerve activity increases after compassionate mental imagery (Kirby et al., 2017). This activity can be assessed non-invasively using an ECG device that measures changes in heart rate (heart rate variability; HRV), which is an index of parasympathetic nervous system functioning.  Previous research has examined the effects of inducing compassionate feelings and then measuring vagus nerve activity (by measuring HRV). However, no published study has demonstrated the association between vagal activity and compassion by modulating the vagus nerve itself. Such studies not only have theoretical implications, but are also potentially valuable in the future development of interventions that employ tVNS or similar technology to augment psychological treatments incorporating compassion-focused techniques (e.g. compassionate mind training; compassion focused cognitive therapy).  In this study, we aim to *directly* test the relationship between vagus nerve activity and compassionate feelings using non-invasive stimulation of the vagus nerve in healthy volunteers. Our own recently completed unpublished related study (Title: The effects of vagus nerve stimulation on compassionate mind training and threat processing; UCL ethics ID: 4277/001) attempted to do this by **comparing** the effects of **active tVNS** **combined with compassionate mental imagery** with **‘sham’ tVNS** **combined with compassionate imagery**. However, that study only used two relatively brief tVNS sessions (only one of which was ‘active’) and evidence of vagal nerve modulation was weak. According to recent research (Yap et al., 2020), our stimulation protocol may have been insufficient to generate behavioural (including subjective) changes. In addition, that study included a compassionate imagery exercise in both the active and sham tVNS conditions, thus preventing us from examining the effects of imagery in isolation.  Our **primary research questions** are therefore:  ***(1)*** Is the tVNS protocol used here (7 stimulation sessions instead of 2, as used in our previous study) associated with reliable physiological (e.g. HRV) changes between lab Sessions 1 and 2?  ***(2)*** Is tVNS sufficient to **generate** compassionate subjective states; are these effects cumulative?  ***(3)*** Does tVNS **augment** the response to compassionate mental imagery compared to control imagery?  Because we are interested in the **interaction between stimulation and the mental imagery task**, we will use a **four group factorial design** in which participants are randomly assigned to **(i) tVNS + control imagery**, **(ii)** **tVNS + compassionate imagery**, **(iii)** **sham-stimulation + control imagery** and **(iv) sham-stimulation + compassionate imagery**. This design will help us establish whether tVNS alone generates compassionate behaviours/feelings and therefore allow us to directly link the effects of activity of the vagus nerve to compassionate feelings. Alternatively, the effects of tVNS on compassionate behaviour(feelings) may only be observed when combined with compassionate imagery (i.e. priming the vagus nerve may enhance the effects of compassionate imagery).  **Secondary questions** relate to:   1. The effects of tVNS and compassionate imagery on recognition of compassionate versus neutral emotional expressions 2. Moderation of effects by trait compassion, mindfulness and historical trauma (these are exploratory analyses intended for hypothesis generation, and will be declared as such in pre-registration documentation). |
| --- | --- | --- |

| \| **B2** \| \| --- \| | **Briefly characterise in simple lay person’s prose the research protocol, type of procedure and/or research methodology (e.g. observational, survey research, experimental). Give details of any samples or measurements to be taken** *(max 500 words).*  **Design**  This is a randomised, controlled experimental study.  **Participants**  Participants will be healthy young volunteers.  **Screening**  Participants will respond to study advertisements which provide a link to study information and basic screening questions (age, sex, confirmation of absence of physical and mental health problems as well as the PHQ-2 and GAD-2 questionnaires to screen for severe anxiety or depression). Participants will provide contact information via the online screening and the researcher will email participants to arrange an additional telephone screening interview. The latter is essential for developing rapport with participants and ensuring proper understanding of the commitment required for the study. Eligible participants will attend two sessions at UCL and perform the between-session tasks on consecutive days.  **Lab Sessions 1 and 2 (1 week apart)**  Sessions 1 and 2 are identical except that additional instructions for ‘at-home’ stimulation are provided at the end of Session 1.  Upon arrival, participants attach the relevant physiological probes (see Appendix V) which will continuously record heart rate. They then complete a series of *trait* questionnaires that assess mood (using the DASS-21 questionnaire), mindfulness, compassion, attachment security and childhood trauma (see Appendix V for full list). They also complete the baseline (i.e. Timepoint 1; T1) emotion recognition task (with simultaneous eye-tracking; see Appendix V) and pre-stimulation *state* measures of self-compassion (SCCS) and positive and negative affect (PANAS; Appendix V).  The researcher then familiarises the participant with the tVNS device and attaches the ear-clip to the participant’s ear (tragus or earlobe, depending on stimulation condition; See Appendix V for further detail) before starting the stimulation threshold-setting procedure. The threshold is set individually for each participant and corresponds to the current level at which s/he experiences a mild tingling sensation. The experimenter will explain the device settings to the participant. Participants then detach the ear-clip, switch the Parasym device off, before reattach the ear-clip and switching the device on and ensuring that the stimulator produces the same sensation as before. This is required to ensure that participants can use the device independently for the at-home stimulations.  Thirty minutes of constant tVNS is applied while the participant relaxes and listens to a standard set of (neutral) music pieces. After this, the emotion recognition/eye tracking task and state questionnaires are repeated (post-stimulation; T2), followed immediately by either the self-compassion or ‘draw-a-face’ imagery tasks (depending on the participant’s random assignment to imagery condition; see below) while stimulation continues. They then complete the final emotion recognition/eye tracking task, state questionnaires (post-imagery; T3) and questions on mental imagery vividness (Appendix V).  Any non-disposable equipment that involves direct contact with the participant’s skin will be disinfected with >70% ethanol solution and placed in a UV-C chamber for 11 minutes before use with the subsequent participant.  At the end of Session 1 (day 1), the experimenter provides instructions on the use of the tVNS device to the participant, and ensures that they understand the importance of retaining the stimulation settings and site of stimulation. The device is very easy to use and verbal instructions will be supplemented with brief written instructions to ensure compliance with the procedure. In fact, the main instructions are to *not modify* the settings from Session 1, and simply attach the ear-clip and switch the device on for the required period, as previously instructed. Participants return for Session 2 (day 8) one week later and repeat the above procedure.  **Between session stimulation and imagery**  From day 2 (the day after Session 1) until day 7 (the day before Session 2), participants use the tVNS device independently. Prior to stimulation they will log on to the Qualtrics study site and complete the baseline state questionnaires on affect and self-compassion. They then either attach the ear-clip to the tragus or the earlobe (depending on randomised condition used in Session 1) and initially stimulate for 30 min. The Qualtrics page will display a visual countdown indicating the required duration of stimulation. To maximise cooperation and minimise disruption to participants, no specific concurrent task is prescribed during the 30 min stimulation, other than suggesting that the participant sits and relaxes/ watches a nature documentary (i.e. activities that are minimally arousing).  After 30 min, participants proceed to the compassionate or control imagery audio instructions (which are the same as those they received on Session 1, according to randomisation) which are played via the Qualtrics site. Participants are free to select the volume level and mode of listening, i.e. via earphones (as long as these do not interfere with the ear-clip) or through their device’s loudspeaker. State affect and self-compassion measures are repeated after stimulation and after the mental imagery task.  **Note**: the Parasym device is a small battery operated ‘straight-to-consumer’ device, **designed to be used at home** independently of additional researcher/clinician instruction (see accompanying product information or details at [https://www.parasym.co/parasym-device-transcutaneous-vagus-nerve-stimulation.html](https://www.parasym.co/)). |
| --- | --- | --- |
|  | *Attach any questionnaires, psychological tests, etc.* *(a standardised questionnaire does not need to be attached, but please provide the name and details of the questionnaire together with a published reference to its prior usage).* |

| \| **B3** \| \| --- \| | **Where will the study take place (please provide name of institution/department)?** If the study is to be carried out overseas, what steps have been taken to secure research and ethical permission in the study country?  The work will be conducted at:   1. The Research Dept Clinical, Educational and Health Psychology ([name]) and 2. The Psychology Department ([name])   Is the research compliant with Data Protection legislation in the country concerned or is it compliant with the General Data Protection Regulation 2018?  N/A. GDPR procures will be followed as required for studies conducted at UCL. |
| --- | --- | --- |

| \| **B5** \| \| --- \| | **How will the results be disseminated, including communication of results with research participants?**  The results will be disseminated in peer reviewed journals, conference presentations, and student dissertations. Participants interested in the findings will be informed of a rough timescale within which these reports might be published and invited to contact the researchers for the published report. |
| --- | --- | --- |

| \| **B6** \| \| --- \| | **Please outline any ethical issues that might arise from the proposed study and how they are be addressed.** *Please note that all research projects have some ethical considerations so do not leave this section blank.*  **Vagus nerve stimulation:** tVNS involves applying a small amount of electrical current (~5 mA) to the outer ear (tragus or earlobe). Participants only feel a mild tingling or pulsing sensation during stimulation. The stimulation ear-clips are easily removed if the participant feels any discomfort. Among the numerous published experimental lab studies in healthy people and in clinical trials, we are not aware of any reports of adverse reactions.  **Physiological measures/attachment of physiological probes:** Every effort has been made to limit skin-to-skin contact between participant and researcher. As such, the researcher will provide written and pictorial instructions on how participants can attach ECG electrodes to their torso themselves. In previous studies we have not found that data quality is adversely affected by participants attaching these devices themselves.  **Questionnaires**: A questionnaire used in this study – the childhood trauma questionnaire - enquires about distressing experiences of trauma (physical, sexual, emotional abuse) and neglect during childhood. The inclusion of this questionnaire is important because one possible moderator of the effects of tVNS (or self-soothing mental imagery) is the capacity to regulate autonomic activity, which can be adversely and enduringly affected by traumatic childhood experiences. We (and many other researchers) have used this questionnaire in numerous studies and have found it to be acceptable to participants. Nonetheless, responding to this questionnaire could potentially evoke unpleasant memories in some participants. As such, there is a specific statement in the participant information sheet stating that questions about difficult experiences from childhood will be asked during the study and that participants should not participate if they are likely to find such questions upsetting. The principal investigator is a clinical psychologist and registered psychotherapist and will be available for support and advice in the unlikely event of participants experiencing distress during the study.  The DASS-21 questionnaires inquire about anxiety and depression. Although we are not intending to recruit participants with significant levels of anxiety or depression, the DASS-21 may identify participants with likely depression and anxiety, which may require treatment. All participants, whether eligible or not, will therefore receive a mental health resource leaflet (attached; Appendix VI) at screening. In order to avoid stigmatising anyone, this leaflet will be given to all participants regardless of whether they show specific symptoms or not. Nonetheless, the researcher will un-intrusively draw participants’ attention to the leaflet at the end of screening if they score in the mild range or above for anxiety or depression. |
| --- | --- | --- |

| **SECTION C DETAILS OF PARTICIPANTS** |
| --- |

| \| **C1** \| \| --- \| | **Participants to be studied**   \| **C1a. Number of volunteers:** \| 140 \| \| --- \| --- \| \| Upper age limit: \| 35 \| \| Lower age limit: \| 18 \|   **C1b. Please justify the age range and sample size:**  Participants must be adults (hence the minimum age of 18). The upper limit will ensure that our sample is directly comparable to previous research in the field, including our recently completed study on tVNS (which used the same age range). In addition, ‘older’ women participants are more likely to experience hormonal changes (e.g. associated with menopause). Given that emotional processing can be affected by ovarian hormone levels, exclusion of older participants will reduce additional variability (noise) resulting from this. Clearly, ‘older’ men must also therefore be excluded to prevent imbalances in ages between sexes.  Sample Size: The sample size is based on pragmatic and statistical considerations. A sensitivity analysis suggests that n=140 will allow us to detect a between group effect size of d=0.48 (alpha=0.05; 1-beta=0.8; two tailed) for a critical comparison between active and sham tVNS groups on self-reported self-compassion (collapsed across imagery condition). This is a plausible effect size based on limited related research (e.g. d=0.6 in Petrocci et al, 2017, who examined the effects of anodal left temporal lobe transcranial Direct Current Stimulation on positive affect). We believe that tVNS’s effects on positive/affiliative mood states will be stronger than those found with tDCS (there is a stronger neurobiological rationale for tVNS), and as such, an effect size at least as large as observed by Petrocci et al (2017) can be expected in the current study. On this basis, an effect size d<0.5 is conservative, but seems appropriate given the uncertainties in the effects of tVNS on psychological functioning. Sensitivity analysis suggests that a lower sample size of n=120 is still sufficient to detect an effect size of 0.52. As such n=140 is aspirational and n=120 is acceptable. |
| --- | --- | --- | --- | --- | --- | --- | --- | --- |

| \| **C2** \| \| --- \| | **Accessing/Using Pre-Collected Data:**  **If you are using data or information held by a third party, please explain how you will obtain this. You should confirm that the information has been obtained in accordance with the General Data Protection Regulation 2018.**  NA |
| --- | --- | --- |

| \| **C3** \| \| --- \| | **Will the research include children or vulnerable adults such as individuals with**  **a learning disability or cognitive impairment or individuals in a dependent or unequal relationship?**  **Yes**  **No**    How will you ensure that participants in these groups are competent to give consent to take part in this study? *If you have relevant correspondence, please attach it.*  N/A |
| --- | --- | --- |

| \| **C4** \| \| --- \| | **Will payment or any other incentive, such as gift service or free services, be made to any research participant?**  **Yes**  **No**    If yes, please specify the level of payment to be made and/or the source of the funds/gift/free service to be used.  Upon completion participants will receive £70-80 (the final amount will be determined after the average time commitment has been determined upon piloting).  Please justify the payment/other incentive you intend to offer.  It is essential to properly compensate participants to ensure they are retained for the duration of the study and feel valued. This will increase the likelihood of compliance, which is especially critical for the between-session (at home) stimulation and imagery tasks. We anticipate that participants will commit 7-8 hr for the entire study. Specifically, they attend two lab sessions (~4 hr total) and complete 45 min of stimulation and imagery on days 2-6 (3.75 hr). The total compensation is based on £10/hr. All participants completing the study will receive the same amount based on the average amount of time taken to complete the study in piloting. |
| --- | --- | --- |

| \| **C5** \| \| --- \| | **Recruitment**  (i) Describe how potential participants will be identified:  Participants will respond to posts about the study. They will voluntarily respond by clicking on a web address which will direct them to study information or contact the researchers by phone to request information.  (ii) Describe how potential participants will be approached:  Participants will not be directly approached by researchers. They will learn about the study via posts on social media (e.g. Facebook); online experiment recruitment sites (e.g. Experimatch; Call for participants), UCL’s psychology participant pool; word-of-mouth; adverts on UCL notice boards; in-house participant mailing lists and flyers.  (iii) Describe how participants will be recruited:  Participants passing the online screening will provide their contact information to allow the telephone screening interview to be arranged. During the phone screening, researchers will provide more details about what is expected of participants and will answer any questions. The researcher will also confirm that participants meet the full eligibility criteria.  If the potential participant meets relevant criteria they will be invited to the first of two experimental sessions at UCL. At the start of Session 1 they will be given a printed copy of the information sheet and will be able to ask any outstanding questions about the study. They will then be asked for their signed consent. In consenting, all participants will be told that they can discontinue participation at any time without having to give a reason. |
| --- | --- | --- |

| \| **C6** \| \| --- \| | **Will the participants participate on a fully voluntary basis?**  **Yes**  **No**  **Will UCL students be involved as participants in the research project?**  **Yes**  **No**  *If yes, care must be taken to ensure that they are recruited in such a way that they do not feel any obligation  to a teacher or member of staff to participate.*  Participant will not be approached by the research team directly. The PI (the only member of staff on the research team who might be considered to be in a position of ‘power’) will have no role in recruiting participants.  **Please state how you will bring to the attention of the participants their right to withdraw from the study without penalty?**  This will be stated on both the information sheet and consent form and reiterated verbally at Session 1. |
| --- | --- | --- |

| \| **C7** \| \| --- \| | **CONSENT**  **Please describe the process you will use when seeking and obtaining consent.**  Participants will first be informed about details of the study via the online study site. After reading this information they will be asked if they wish to proceed to basic online eligibility screening. If eligible, based on basic criteria, a further telephone screening/information telephone call will be arranged with the researcher (the information sheet will be emailed to the participant prior to the telephone screening) to ensure full eligibility. Confirmation that the participant has read and understood the study information will be obtained by the researcher during this phone screening, and the researcher will ensure that participants are informed of and understand what is expected of them for the study. During this screening, the researcher will emphasise participants’ right to withdraw at any time without giving a reason.  If eligible, participants attend Session 1, at which they must confirm again that they have read and understood the information sheet prior to signing the study consent form.  *A copy of your participant information sheet(s) and consent form(s) must be attached to this application. For your convenience proformas are provided in Appendix I. These should be filled in and modified as necessary.*  In cases where it is not proposed to obtain the participants informed consent, please explain why below.  N/A |
| --- | --- | --- |

| \| **C8** \| \| --- \| | **Will any form of deception be used that raises ethical issues? If so, please explain.**  Although frank deception will not be used, it is necessary to conceal aspects of the study design and aims from participants because expectancy effects could invalidate the findings. In particular, participants are only informed that stimulation will be applied to the “outer ear” rather than the specific locations of stimulation (tragus or earlobe) to which they may be assigned. This is a *critical requirement* for the study, because if participants are told in advance that only one of two stimulation sites is expected to be ‘active’, they can easily obtain information about the active site and blinding would be removed. Interpretation of the findings would then be impossible as we would not be able to disentangle ‘real’ effects from expectancy-induced changes. As such participants will be ‘blind’ to the nature of the *active* stimulation.  On balance, given the need for incomplete disclosure of our aims and hypotheses, we believe it is necessary to include a statement on the use of deception in PIL. |
| --- | --- | --- |

| \| **C9** \| \| --- \| | **Will you provide a full debriefing at the end of the data collection phase?**  **Yes**  **No**  If ‘No’, please explain why below.  Full debriefing will occur at the end of session 2, including disclosure about the concealed aspects noted above. Participants will be requested not to discuss these debriefing details with others. |
| --- | --- | --- |

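### Home listening mode is a free choice limited by the ear-clip, whose site defines active and sham, so audio delivery on the home days may differ between those arms

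*Protocol*

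**What the plan says.** Protocol B2 (Between session stimulation and imagery) sets the home routine. On clip placement: "They then either attach the ear-clip to the tragus or the earlobe (depending on randomised condition used in Session 1"). The imagery audio is played through the Qualtrics site, with instructions "which are the same as those they received on Session 1, according to randomisation". Volume is left to the participant, and so is the "mode of listening, i.e. via earphones (as long as these do not interfere with the ear-clip"). The alternative, open to every arm, is a loudspeaker. The wording is the same for all four arms and names neither clip site.

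State affect and self-compassion are taken at home before stimulation, after it, and after imagery. Listening mode and volume are not among the home measures described. B2 counts home days 2 to 7 (six sessions) and C4 counts days 2 to 6 (five). Either way, home sessions outnumber the two lab sessions.

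For the lab, B2 says "Sessions 1 and 2 are identical except that additional instructions for ‘at-home’ stimulation are provided at the end of Session 1". The free choice of listening mode is stated only for home use.

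Primary question 3 in B1 asks whether stimulation augments "the response to compassionate mental imagery compared to control imagery". B1 justifies the four-group factorial design by interest in the interaction of stimulation with imagery. The sample size in C1b rests on a different comparison: active versus sham on self-reported self-compassion, pooled over the two imagery tasks.

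**The concern.** Permission to use earphones depends on an object whose position is the randomised stimulation factor. A rule worded alike for every arm can therefore act differently by arm. The tragus borders the opening of the ear canal, where an earphone sits, and the earlobe hangs below it. If the proviso is followed, more participants in the tragus arms are likely to use the loudspeaker.

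Listening mode would then be a consequence of the stimulation allocation. Randomisation would not balance it, and because it arises after randomisation, ordinary covariate adjustment would not cleanly remove it. If it is not recorded, no later analysis can examine it at all.

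At stake is how to read a difference between active and sham scores after home imagery. Part of it could come from how the audio was delivered and not from stimulation. B1 also asks whether effects are cumulative, so the home sessions matter to the primary questions.

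**Working it through.** **1. The plan's own figure.** C1b gives d = 0.48 at n = 140 and d = 0.52 at n = 120 (alpha 0.05 two-tailed, power 0.8). For two equal groups the detectable effect by the normal approximation is (1.960 + 0.842) × √(2/n per group). With 70 per group this is 0.474 (noncentral t: 0.477). With 60 per group it is 0.511 (0.516). Both stated figures are reproduced.

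**2. Inputs that the protocol does not give.** Two are needed, and both are assumptions:
- g, the active-versus-sham gap in the share using earphones: 0.30 to 0.70, middle 0.50.
- m, the effect of listening mode on the post-imagery score: 0.1 to 0.4 SD, middle 0.2 SD.

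The bias is g × m. The power losses below further assume that earphones help imagery, so that the bias runs against active stimulation. The protocol does not say so.

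**3. Active versus sham on home post-imagery scores, pooled over imagery** (70 v 70, two-sided t-test, true d = 0.48):

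| g | m (SD) | Bias g × m | d seen | Power |
|---|---|---|---|---|
| 0 | any | 0 | 0.48 | 80.5% |
| 0.30 | 0.1 | 0.03 | 0.45 | 75.3% |
| 0.50 | 0.2 | 0.10 | 0.38 | 60.7% |
| 0.70 | 0.4 | 0.28 | 0.20 | 21.7% |

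**4. Question 3, the interaction.** This is (active − sham) under compassionate imagery minus (active − sham) under control imagery. Both imagery arms within a stimulation condition share the same clip site and listening rule. With the same g in both:

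bias = g × m(compassionate) − g × m(control) = g × [m(compassionate) − m(control)].

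If mode acts equally on the two tasks the bracket is zero, and so is the bias, whatever g is.

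If the bracket is 0.2 SD and g is 0.50, the bias is 0.10 SD. With equal allocation (assumed; 35 per cell) the standard error is √(4/35) = 0.338 SD, and the interaction detectable with 80% power is 2.802 × 0.338 = 0.95 SD. After a bias of 0.10 against it, (0.95 − 0.10)/0.338 = 2.51, and 2.51 − 1.96 = 0.55, which gives power of about 71%. With no true interaction, the same bias moves the rejection rate from 5% to 6.0%.

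**5. Lab outcomes.** Session 1 precedes all home use, so its scores cannot be affected. Session 2 could be affected only if differently delivered home practice carries over.

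**The case against.** The strongest objection is that question 3 is an interaction and that a mode effect common to both imagery tasks cancels. This stands. A reader might infer that the rule confounds question 3, but the documents do not support that: it would need mode to act differently on compassionate and control imagery, on which the protocol is silent. Nor do the power losses in the pooled comparison describe question 3. The cancellation does not, however, protect the pooled active-versus-sham comparison where that uses home post-imagery scores.

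Second, the protocol nowhere says that earphones interfere at the tragus and not at the earlobe, or what type of earphone is meant. It describes one clip on one ear, so an earphone in the other ear seems already allowed. This also stands, and it may make the gap small. The anatomical inference is reasonable, but it remains an inference.

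Third, a reader might infer that earphones pressing on a tragus clip would disturb stimulation in the active arms. That is what the proviso forbids, so this route requires the rule to be broken.

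Fourth, B2 is a lay summary that points to an appendix and to written participant instructions, neither of which is at hand. Listening mode might be specified or recorded there. The point is therefore limited to the text shown.

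**Conclusion.** A narrow point holds. In the text at hand, home listening mode is neither standardised nor listed as recorded, and the one limit on it is tied to the object that distinguishes active from sham. A systematic difference in audio delivery between those arms on the home days is therefore possible. Performance bias is a better name for it than confounding, since it would arise after randomisation.

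Its size is unknown and probably small. The middle assumptions give 0.10 SD. In the pooled comparison of home post-imagery scores, power for d = 0.48 then falls from about 80% to 61%. For the interaction, power for 0.95 SD falls from 80% to about 71%, and only if the 0.2 SD is the difference in mode effect between the two tasks. The 22% at the far end needs both assumed inputs at their maximum.

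A reader might also infer that the bias must run against tVNS. That rests on earphones giving the better imagery response, which no part of the protocol states. This is a cheap improvement to make before recruitment, not a flaw that undermines the primary questions.

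**What to change.** In B2 and the home instructions, replace the free choice with one listening mode for all four arms that does not depend on clip site. Two candidates are the device loudspeaker for everyone, or a single earphone in the ear without the clip for everyone.

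Add one Qualtrics item to each home session recording how the audio was heard, so that adherence can be described by arm.

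The cost is one sentence and one item, with no added visits or staff. The downside is less privacy (loudspeaker) or less choice for some participants.
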